#### Sample Size and Randomization

A previous study conducted in the Asia-Pacific region reported that SBP is an important marker of risk of CVD in people with and without diabetes. A given reduction in SBP is likely to have similar relative effect on reducing the risk of a cardiovascular event, regardless of diabetes status [21]. SBP is therefore being set as the primary outcome and for sample size calculation.

A previous local study on a Tai Chi program reported a mean reduction of 15.6 mmHg (standard deviation, SD = 7.9) in the intervention group and a mean increase of 6.4 mmHg (SD = 10.5) in the control group [22]. Another pre-post study showed a mean reduction of 8.7 mmHg (SD = 15.6) in SBP after receiving a walking program in obese postmenopausal women [23]. We based our sample size calculation conservatively on discriminating among a mean SBP reduction of 15.5 mmHg in the Tai Chi group, 4.0 mmHg in the control group, and 9.75 mmHg (the grand mean) in the walking group. Further conservatively assuming an SD of 20.0, G*Power gives that 61 subjects per arm will be needed to achieve a power of 80% at a significance level of 5%. To further take into account a potential attrition rate of 25% [12], 246 subjects (82/arm) will be targeted.

A computer-based randomizer will be used for random allocation of subjects [24]. Eligible subjects will be randomly assigned to the three groups in 1:1:1 ratio according to their sequence of enrolment into the study and the corresponding sequentially listed group identifiers generated by the randomizer in advance. The random group identifiers list will be stored in a password-protected computer and only be accessible by the staff who are responsible for group allocation.

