### 2.6. Data Analysis

(1)For demographic data, frequency and percentage will be used to summarize and present categorical variables, whereas mean and SD will be used for continuous variables. Normality of continuous variables will be examined using skewness and kurtosis statistics and normal probability plot. The baseline characteristics among the three groups will be compared using chi-square test and one-way analysis of variance (ANOVA).(2)Generalized estimating equations (GEE) models with appropriate link function and distribution assumption, will be used to compare the changes in outcome variables across time among the three groups with adjustment for those baseline characteristics showing statistically significant differences among the groups. In the GEE model for each outcome, two dummy variables will be set to correspond the three groups with the control as reference. Another three dummy variables will be set to represent the four time points (T1 to T4) with the baseline (T1) as the reference. The interaction-terms of group by time will also be included in the GEE models to assess the differential changes of the outcomes across time and between group. All primary and secondary outcomes will be compared between the three groups on the basis of the intention-to-treat (ITT) principle. The GEE model can account for intra-correlated repeated measures data and accommodate missing data caused by dropouts, provided the data is missing at random [34], and thus is particularly suitable for ITT analysis, without the need for imputation of missing data.

All data analyses will be performed using the latest version of IBM SPSS (IBM Corp., Armonk, NY, USA). Level of statistical significance will be set at 0.05.

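### Baseline covariates entered as main effects, the natural reading of section 2.6, barely act on the group-by-time contrasts that the plan calls adjusted

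*Protocol article*

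**What the plan says.** Section 2.6 (Data Analysis) states the aim and then the terms of the model.

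- Aim: GEE models "will be used to compare the changes in outcome variables across time among the three groups".
- Covariates: this comparison is to be made "with adjustment for those baseline characteristics showing statistically significant differences among the groups".
- Group: "two dummy variables will be set to correspond the three groups with the control as reference".
- Time: "Another three dummy variables will be set to represent the four time points (T1 to T4) with the baseline (T1) as the reference". T1 is therefore one of the responses.
- Interaction: "The interaction-terms of group by time will also be included in the GEE models to assess the differential changes of the outcomes". No other interaction is named.
- Link: "Generalized estimating equations (GEE) models with appropriate link function and distribution assumption". Neither the link nor the working correlation is fixed.
- Missing data: no imputation; GEE is said to "accommodate missing data caused by dropouts, provided the data is missing at random".

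The section on sample size and randomisation plans for SBP reductions of 15.5, 9.75 and 4.0 mmHg (Tai Chi, walking, control), an SD of 20.0, 25% attrition and 82 participants per arm.

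**The concern.** The comparison of interest is the difference between arms in change from T1, and it is read from the group-by-time terms. A baseline characteristic has one value per participant at all four visits. As a main effect it moves the fitted mean by the same amount at T1, T2, T3 and T4, so it disappears when T1 is subtracted. What it adjusts is the group main effect, that is, the difference at baseline, which is not the trial's question.

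At stake is a covariate that differs between arms by chance and also predicts how much blood pressure changes. Its effect stays in the Tai Chi, walking and control contrasts, and a reader told that they are adjusted would assume otherwise. This does not depend on how the covariates are selected: a well-chosen covariate entered this way would do no better.

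**Working it through.** **The plan's own figures.** Effect size f = sqrt[(5.75² + 0² + 5.75²)/3]/20 = 0.2347. The one-way ANOVA F test at 5% has power 80.5% with 60 per arm and 81.2% with 61, so the stated 61 is reproduced within rounding. 61/0.75 = 81.3, hence 82 per arm and 246 in total. No covariate adjustment was assumed, so the sample size is unaffected by this point.

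**Algebra.** Take an identity link, complete data and one working correlation for all participants. The model is E(Y_it) = μ(g,t) + βx_i, with a free mean for every group and visit.

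1. Solving for the cell means gives μ̂(g,t) = Ȳ(g,t) − β̂·x̄(g).
2. The change is μ̂(g,t) − μ̂(g,1) = Ȳ(g,t) − Ȳ(g,1), whatever β̂ is. The group-by-time terms equal the raw differences in mean change.
3. With a coefficient per visit, β_t, the change becomes Ȳ(g,t) − Ȳ(g,1) − (β̂_t − β̂_1)·x̄(g). Only now does the covariate correct the contrast.

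**Simulation.** 82 per arm, four visits, 150 replicates per scenario. The estimand is Tai Chi versus control at T4, true value −15.5 + 4.0 = −11.5 mmHg. Values assumed, not taken from the protocol: covariate imbalance 0.45 SD in the Tai Chi arm, 6 mmHg per SD on level, −3 mmHg per SD on change, between-participant SD 12, residual SD 10.

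Complete data, identity link (same under independence and exchangeable correlation):

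| Model | Mean estimate | Mean SE |
|---|---|---|
| No covariate | −12.92 | 2.237 |
| Covariate main effect | −12.92 | 2.237 |
| Covariate by time | −11.55 | 2.221 |

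The first two rows agreed in every replicate. The expected residual error is −3 × 0.45 = −1.35 and the observed error is −12.92 + 11.5 = −1.42; the Monte Carlo error is about 2.237/√150 = 0.18. In one dataset the group main effect moved from 3.63 to 1.81 while the group-by-time terms did not move.

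Mean absolute shift of the T4 contrast (mmHg) from adding the covariate main effect, with dropout:

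| Dropout | Exchangeable | Independence |
|---|---|---|
| About 25%, completely random | 0.08 | 0.27 |
| About 25%, depends on the covariate | 0.13 | 0.43 |
| About 31%, depends on the covariate differently by arm | 0.61 | 2.02 |

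The exchangeable shifts in the first two rows are 3% and 5% of a standard error (0.0754/2.491 and 0.1338/2.528). With a log link and complete data, the T4 term in one dataset moved from −0.0883 to −0.0876.

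**What could remain in a contrast.** Take the smallest imbalance at which a one-way ANOVA with 82 per arm gives p = 0.05, where F(2, 243) = 3.033.

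- Third arm midway between the extremes: d = sqrt(4 × 3.033/82) = 0.385 SD.
- Third arm equal to one extreme: d = sqrt(3 × 3.033/82) = 0.333 SD.

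Residual = r × SD of change × d, with r assumed to be 0.1 to 0.3.

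- SD 20: 0.1 × 20 × 0.333 = 0.67 to 0.3 × 20 × 0.385 = 2.3 mmHg. That is 12% to 40% of the planned 5.75 mmHg Tai Chi–walking difference, or 6% to 20% of the 11.5 mmHg Tai Chi–control difference.
- The SDs of 7.9 to 15.6 from the earlier studies quoted in the sample size section: 0.1 × 7.9 × 0.333 = 0.26 to 0.3 × 15.6 × 0.385 = 1.8 mmHg.

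**The case against.** The strongest reply is that the defect is inferred. Section 2.6 never says that the covariates enter as main effects only, and a journal article may leave such detail to the full protocol or SAP. This stands in part: main-effect entry is a reading. But the section does list the model's terms, names one interaction, and promises an adjusted comparison of changes. Read as written, the listed model does not deliver that.

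A reader might infer that the reported contrasts are simply unadjusted. The document does not support that without conditions. It leaves the link open and expects 25% attrition, and with incomplete data the main effect does move the estimate. It can help when missingness depends on the covariate: with dropout that differed by arm, it brought the mean from −14.42 to −12.41 under independence and from −12.73 to −12.12 under exchangeable correlation (true −11.5). That works through missingness, and covariate-by-time terms came closer still (−11.55 and −11.61).

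A reader might also infer that the trial has no other protection against imbalance, or that its estimator is biased. Neither follows. Allocation is randomised 1:1:1, so the contrast is unbiased over randomisation, and differencing from T1 already removes any constant effect of a covariate on blood pressure level. What remains is an error conditional on a chance imbalance in a predictor of change. Nor is there a material loss of precision: covariate-by-time terms lowered the SE by only 0.7% in the simulation (2.237 to 2.221).

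**Conclusion.** The point holds in a limited form. On the natural reading of section 2.6, the promised adjustment has no effect on the group-by-time contrasts with an identity link and complete data. It has almost none (about 0.1 mmHg) with roughly 25% dropout unrelated to the covariate and an exchangeable structure. Larger shifts occur under independence correlation or arm-specific, covariate-dependent dropout.

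The consequence is a mislabelled result: a chance imbalance in a covariate that predicts change would stay in a contrast described as adjusted. The illustrative 0.7 to 2.3 mmHg rests on an assumed imbalance of 0.33 to 0.38 SD and an assumed correlation of 0.1 to 0.3, with the plan's SD of 20; it is smaller with the SDs from the earlier studies. The protocol gives no figure for the imbalance or the correlation, so the range shows scale and is not a forecast. The change is worth making because it costs so little.

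**What to change.** State in section 2.6 how the adjustment covariates enter, by one of two routes, and report the group contrasts from that model.

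1. Keep T1 as a response and enter each covariate both as a main effect and by time (covariate × T2, × T3, × T4).
2. Model T2 to T4 as the responses, with the baseline value of the outcome and the covariates as predictors.

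The second route is an alternative and not an equivalent of the first, and it must include the baseline outcome. Without it the model compares follow-up levels instead of changes; in simulated datasets its estimates then differed from the covariate-by-time model by about 2 mmHg on average.

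The first route costs one sentence and three extra parameters per covariate, which is minor with 246 participants. The sample size does not change.

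### The planned GEE compares raw changes from baseline and so gives up precision that adjusting for the T1 value already collected would provide at almost no cost

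*Protocol article*

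**What the plan says.** Section 2.6 (Data Analysis) sets out one GEE structure for every outcome. For the arms, "two dummy variables will be set to correspond the three groups with the control as reference". For time, "three dummy variables will be set to represent the four time points (T1 to T4) with the baseline (T1) as the reference". Group-by-time interactions are added to capture differential change. T1 is therefore part of the response, each arm has its own baseline mean, and the treatment effects are the interactions.

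The only covariate adjustment foreseen in that section is for baseline characteristics that turn out significantly different between arms. The T1 value of the outcome is not named as a covariate, and the baseline means are not constrained to be equal, although patients are "randomly assigned to the three groups in 1:1:1 ratio" (Sample Size and Randomization). Section 2.5 confirms that T1 measurements are taken on everyone.

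On size, the article states that "SBP is therefore being set as the primary outcome and for sample size calculation". It assumes mean reductions of 15.5 mmHg (Tai Chi), 9.75 mmHg (walking) and 4.0 mmHg (control), then adds: "Further conservatively assuming an SD of 20.0". This gives 61 per arm and, with a "potential attrition rate of 25% [12], 246 subjects (82/arm) will be targeted".

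**The concern.** With a saturated group-by-time model, an identity link and complete data, each interaction equals the between-arm difference in mean change from T1. A chance difference between arms at baseline is then subtracted in full, not in proportion to how well baseline predicts follow-up. Randomisation already makes the expected T1 means equal, so the two group main effects estimate differences known to be zero, and their sampling error carries into the treatment contrasts.

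What is at stake is precision. It matters most for Tai Chi versus brisk walking, which the Abstract, Introduction and Conclusions present as the central comparison. On the article's own assumptions this is the smaller contrast to be detected (15.5 − 9.75 = 5.75 mmHg).

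**Working it through.** **Inputs from the article.** Means 15.5, 9.75 and 4.0 mmHg; SD 20, read as the SD of change because it is applied to reductions; 61 per arm after attrition and 82 per arm enrolled; significance level 5%.

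**Assumptions of this check.** Two-sided tests; equal variance s² at T1 and follow-up; baseline-to-follow-up correlation ρ of 0.3, 0.5 or 0.7, since the article gives none.

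**1. The article's own figure.** For the three-arm F test, the noncentrality is n × Σ(mean − 9.75)² / 20² = 61 × (5.75² + 0² + 5.75²) / 400 = 61 × 66.125 / 400 = 10.08. Power is 81.2% at 61 per arm and 80.5% at 60. Attrition: 61 / 0.75 = 81.3, so 82 per arm and 246 in total. The target is reproduced to within a patient per arm.

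**2. What the model estimates.** In simulated complete data (61 per arm, ρ = 0.5, 200 replicates), the planned group-by-T2 term equalled the raw difference in mean change in every replicate, under both independence and exchangeable working correlations. Adding the T1 value as a time-constant covariate left the term unchanged. The section 2.6 adjustment clause would therefore not recover the precision even if it happened to pick up baseline blood pressure.

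**3. Complete data.** Per subject, Var(change) = 2s²(1 − ρ) and Var(adjusted) = s²(1 − ρ²). The ratio is (1 + ρ)/2:
- ρ = 0.3: 0.65
- ρ = 0.5: 0.75
- ρ = 0.7: 0.85

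**4. With the planned attrition.** Take m = 82 per arm at T1 and n = 61 at one follow-up, with a working correlation that uses the T1 data of those who leave. Per arm:
- planned: s²[(1 − ρ²)/n + (1 − ρ)²/m]
- adjusted: s²(1 − ρ²)/n
- ratio: (1 + ρ) / [(1 + ρ) + (1 − ρ)(n/m)], with n/m = 61/82 = 0.744

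Holding the change SD at 20 gives s² = 400 / [2(1 − ρ)]. Example for ρ = 0.5: s² = 400. The planned variance is 400 × (0.75/61 + 0.25/82) = 6.14, so the SE of a difference is √(2 × 6.14) = 3.50. The adjusted variance is 400 × 0.75/61 = 4.92, so the SE is 3.14. Power is for 5.75 mmHg by noncentral t.

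| ρ | Variance ratio, complete | Variance ratio, 25% dropout | SE planned → adjusted, dropout (mmHg) | Power planned → adjusted, dropout |
|---|---|---|---|---|
| 0.3 | 0.65 | 0.71 | 3.46 → 2.92 | 38% → 50% |
| 0.5 | 0.75 | 0.80 | 3.50 → 3.14 | 37% → 44% |
| 0.7 | 0.85 | 0.88 | 3.55 → 3.34 | 36% → 40% |

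A pure change-score analysis of 61 completers per arm has 35% power. If nobody dropped out (82 per arm), power would go from 45% to 62%, 56% and 51%.

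**5. Simulation with dropout.** With 82 per arm and 25% lost after T1, the adjusted-to-planned variance ratio under an exchangeable working correlation was about 0.83 at ρ = 0.5 (200 replicates) and 0.91 at ρ = 0.7 (150 replicates). These agree with step 4 within what so few replicates can resolve, and they confirm that the complete-data ratios are too favourable here.

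**6. A trap in the remedy.** If the group main effects are dropped under an independence working correlation, the contrast becomes a follow-up-only comparison. Its variance relative to change scores is s² / [2s²(1 − ρ)] = 1/[2(1 − ρ)]: 0.71, 1.00 and 1.67 at ρ = 0.3, 0.5 and 0.7. At the highest of these correlations it is clearly worse than the plan.

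**The case against.** The strongest reply is that nothing here is an error. The planned contrast is unbiased under randomisation, its tests are valid, and the article is consistent: it aims to compare changes, sizes the trial on reductions and analyses changes. All of that stands, and it limits the point to efficiency.

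Two further objections also stand in part. The gain depends on a correlation the article does not give, and it vanishes as ρ approaches 1. The power figures also rest on an SD of 20 that is deliberately high: the SDs the article cites are 7.9, 10.5 and 15.6, and at 10.5 the unadjusted power for 5.75 mmHg at 61 per arm would be 85%. The variance ratios do not depend on that SD.

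A reader might infer more than the documents support:
- **That selection on high blood pressure biases the comparison through regression to the mean.** It acts equally on randomised arms in expectation. What remains is the chance-imbalance variance already counted above.
- **That adjustment is worth a third more patients at ρ = 0.5.** That is the complete-data figure (1/0.75 = 1.33). With the planned attrition it is about a quarter (1/0.80 = 1.25).
- **That the sample size is wrong.** It reproduces.

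**Conclusion.** The point holds as a loss of precision in a model the article states explicitly; it is not a bias or an invalid test. Relative to the plan, adjusting for the T1 value would cut the variance of a treatment contrast by about 29%, 20% or 12% at ρ = 0.3, 0.5 or 0.7 with the planned 25% attrition, and by 35%, 25% or 15% in complete data. For Tai Chi versus walking this is worth roughly 12, 7 or 4 percentage points of power at a change SD of 20. It would not make that comparison well powered under the article's assumptions.

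The result assumes equal variances at T1 and follow-up, an identity link, and a GEE whose working correlation uses the T1 data of those who leave. The change is worth making because the data are already collected and the cost is very small.

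**What to change.** For each continuous outcome measured at T1, prespecify one of two models:

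- **Covariate version.** Use T2 to T4 as the response, with the T1 value and its interaction with time as covariates, fixed in advance and not conditional on a baseline significance test.
- **Common-baseline version.** Keep T1 in the response, drop the two group main effects so that all arms share one T1 mean, keep the group terms at T2, T3 and T4, and specify a non-independence working correlation, for example unstructured. Do not use this version with an independence working correlation.

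Report adjusted differences at T2, T3 and T4.

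The cost is a small change to the model specification, with the same patients, visits and software. The covariate version has one drawback: it leaves out participants with no post-baseline value, which needs a comment given the intention-to-treat aim in section 2.6. The common-baseline version retains them.

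### Section 2.6 states the wrong missing-data condition for GEE: unweighted GEE is not in general valid under missing at random, so the stated reason for needing no imputation fails

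*Protocol article*

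**What the plan says.** Section 2.6 of the protocol article sets one GEE model per outcome: "Generalized estimating equations (GEE) models with appropriate link function and distribution assumption, will be used to compare the changes in outcome variables". The mean model has group, time and group-by-time terms, and baseline is one of the modelled outcome times: "Another three dummy variables will be set to represent the four time points (T1 to T4) with the baseline (T1) as the reference". Covariates enter by a significance rule: "with adjustment for those baseline characteristics showing statistically significant differences among the groups". The analysis principle is stated as "All primary and secondary outcomes will be compared between the three groups on the basis of the intention-to-treat (ITT) principle".

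On dropout, the section says that GEE can "accommodate missing data caused by dropouts, provided the data is missing at random [34], and thus is particularly suitable for ITT analysis". It concludes that the analysis can proceed "without the need for imputation of missing data". It names no weights and no working correlation.

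The section on sample size and randomization allows for loss to follow-up: "To further take into account a potential attrition rate of 25% [12], 246 subjects (82/arm) will be targeted".

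**The concern.** The sentence on dropout is a chain of reasoning: GEE is valid under missing at random (MAR), so it suits an intention-to-treat analysis, so imputation is not needed. The first link is wrong for ordinary GEE.

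Unweighted estimating equations average over whoever is observed. They are consistent in general only if dropout is unrelated to the outcomes (missing completely at random, MCAR) or depends only on covariates in the mean model. MAR validity belongs to likelihood-based models, multiple imputation and suitably weighted GEE.

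The covariate route does not help here. Baseline SBP is a modelled response, not a covariate, and other characteristics enter only if they differ significantly between arms, whether or not they predict dropout.

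At stake is the between-arm change in SBP, the outcome used for sample size, and in particular Tai Chi against walking, which is the trial's main question. Dropout that differs by arm is plausible. Section 2.3 assigns supervised classes twice a week, home walking, or no exercise, and section 2.3.1 itself links intensive intervention to dropout and high attrition to threatened validity.

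**Working it through.** **The plan's own figures.** A one-way ANOVA F test with mean reductions of 15.5, 9.75 and 4.0 mmHg, SD 20 and alpha 0.05 needs 60 per arm (power 80.5%); the stated 61 gives 81.2%. Inflation: 61 / (1 − 0.25) = 81.3, rounded up to 82, and 82 × 3 = 246. The sample size is reproduced, and this point does not change it. The planned contrasts are 15.5 − 4.0 = 11.5 mmHg (Tai Chi against control) and 15.5 − 9.75 = 5.75 mmHg (Tai Chi against walking).

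**Why independence GEE can fail under MAR.** With saturated group-by-time terms, no covariates and an independence working correlation, the fitted mean at each visit is the mean of those attending. The T1 mean still includes later dropouts. In one arm with dropout fraction *d*:

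bias at T4 = mean(attenders) − mean(all) = *d* × [mean(attenders) − mean(dropouts)].

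At *d* = 0.25, a bias of −2.4 to −2.9 mmHg needs dropouts whose T4 SBP would have been about 10 to 12 mmHg higher than that of attenders (2.42 / 0.25 = 9.7; 2.88 / 0.25 = 11.5), or 0.48 to 0.58 of an SD of 20.

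**Simulation.** Inputs from the article: four visits, SD 20 (taken as the SD at each visit), 25% cumulative dropout by T4, and the planned mean changes. Assumptions, because the article gives no values: within-person correlation exchangeable 0.6 or AR(1) 0.7; monotone dropout depending only on the previous observed SBP, which is MAR; log-odds slope 1 per SD. There were 300,000 people per arm, so the results show bias and not sampling error. Entries are the bias in mmHg in the Tai Chi minus control change at T4 (true value −11.5). Columns after the first two are GEE by working correlation, then a likelihood-equivalent analysis.

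| Dropout scenario | True correlation | Independence | Exchangeable | AR(1) | Unstructured | Likelihood |
|---|---|---|---|---|---|---|
| Same in all arms, 25% | Exch. 0.6 | −0.04 | −0.05 | −0.04 | −0.05 | −0.05 |
| Same in all arms, 25% | AR(1) 0.7 | −0.09 | −0.08 | −0.08 | −0.08 | −0.09 |
| SBP-dependent in Tai Chi only, 25% per arm | Exch. 0.6 | −2.88 | −0.02 | −1.06 | −0.03 | 0.03 |
| SBP-dependent in Tai Chi only, 25% per arm | AR(1) 0.7 | −2.42 | 0.37 | −0.04 | −0.03 | 0.03 |
| Same slope, rates 35/25/15% | Exch. 0.6 | −2.29 | −0.05 | −0.92 | −0.07 | 0.06 |
| Same slope, rates 35/25/15% | AR(1) 0.7 | −1.95 | 0.26 | −0.13 | −0.10 | 0.01 |
| Opposite slopes, exercise arms vs control | Exch. 0.6 | −5.89 | −0.36 | −2.49 | −0.42 | −0.12 |
| Opposite slopes, exercise arms vs control | AR(1) 0.7 | −4.84 | 0.61 | −0.32 | −0.26 | 0.09 |

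Under MCAR dropout every method was within about 0.1 of zero. Negative values flatter Tai Chi, because in these runs people with high SBP leave that arm; a reversed slope would reverse the sign.

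**Tai Chi minus walking at T4 (true −5.75), independence GEE.** Dependence in Tai Chi only: −2.88 or −2.43. Rates 35/25/15%: −1.13 or −0.82. Opposite slopes in the two exercise arms, run separately at SD 15: 3.8 mmHg in size, which scales to 3.8 × 20 / 15 = 5.1 at SD 20.

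**Weaker dependence.** With one arm affected and independence GEE, slopes of 0.25 and 0.5 per SD gave biases of about 0.7 and 1.3 to 1.6 mmHg.

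**Against sampling error.** With 61 completers per arm and correlation 0.6, the SD of change is 20 × √(2 × 0.4) = 17.9, and the standard error of a between-arm change is 17.9 × √(2 / 61) = 3.2 mmHg.

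**The case against.** The strongest reply is that the large figures need three things together: dropout that depends on SBP, a difference in that dropout between arms, and an independence working correlation.

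- **Working correlation.** The article does not name independence, and an article may leave the structure to the full protocol or SAP. With a correct or unstructured structure the bias is about 0 with dependence in one arm and 0.3 to 0.4 mmHg with opposite mechanisms.
- **Dropout.** Nothing in the article says that dropout depends on SBP. Sections 2.3.1 to 2.3.3 describe measures that may even it out: training limited to three months, weekly calls to walkers, and social gatherings for the walking and control arms. The 25% is a planning allowance, not a forecast.
- **Size.** At weaker slopes the bias is below one standard error.

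All of this stands and limits the expected size. It does not rescue the sentence. The point is not that a working correlation is missing. The article asserts a validity condition that is wrong in general and rests the lack of imputation on it, and later detail would leave that assertion wrong.

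A reader might infer more, and the documents do not support it:

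- That the SBP contrasts will be biased. They can be, under the conditions above.
- That imputation is forbidden. The article says only that it is not needed, which leaves room for sensitivity analyses.
- That GEE always needs MCAR. That is too blunt for a continuous outcome with a well-chosen working correlation.
- That every outcome is continuous. Section 2.4.2 includes frequency of self-practice, which is a count.

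**Conclusion.** The concern holds in this form: section 2.6 states a wrong condition for the validity of unweighted GEE and uses it to justify an analysis without imputation. None of the features that would make the conclusion safe is committed to in the article.

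If dropout depends on earlier SBP differently by arm, an independence working correlation could bias the T4 between-arm change by roughly 1 to 3 mmHg. At the upper end, 2.9 mmHg is 25% of the 11.5 mmHg contrast and 50% of the 5.75 mmHg contrast. Opposite mechanisms could bring it to 5 to 6 mmHg. An exchangeable or unstructured structure keeps it to about 0.6 mmHg or less in these scenarios. A misspecified AR(1) structure leaves about 1 mmHg with one arm affected or unequal rates, and up to 2.5 mmHg with opposite mechanisms. If dropout is the same in all arms, the bias cancels.

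These sizes rest on assumed correlations and dropout slopes. That the stated condition is wrong does not depend on them.

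**What to change.** 1. Correct the sentence in section 2.6. Unweighted GEE requires dropout that is completely at random or depends only on covariates in the model. For continuous outcomes it is nearly unbiased under MAR only with a correctly specified or unstructured working correlation.
2. For SBP, diastolic pressure and the other continuous outcomes, prespecify a likelihood-based mixed model for repeated measures with the same group, time and group-by-time terms, an unstructured within-person covariance and all observed data. SPSS provides it. Four visits need 4 variances and 6 covariances.
3. Alternatively, keep GEE and prespecify inverse-probability-of-dropout weights or multiple imputation, with arm and earlier outcome values in the dropout or imputation model.
4. GEE with a suitable link may stay for count outcomes such as practice frequency, with weights or imputation for dropout.

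Settle this before outcome data are seen. The cost is a few sentences, slightly more analysis work and a normality assumption for the mixed model. No participants, visits or new software are needed. None of these options protects against dropout that depends on unobserved SBP.
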